### Study population, screening, and randomization

Patients with LARC are eligible for enrollment in this trial. They will be identified by the investigators and referred to the institutional multidisciplinary team for eligibility verification. The primary investigator will take charge of the final enrollment based on the inclusion/exclusion criteria (Table 1). Eligible patients who are willing to participate receive details of the study. After providing written informed consent at each hospital, the participants will be randomly assigned to either Arm A (experimental arm: SCRT plus mFOLFOX6) or Arm B (control arm: CRT). Block randomization at a ratio of 1:1 will be performed and managed by the central clinical research coordinator.

**Table 1 Tab1:** Inclusion and exclusion criteria

Inclusion criteria	Exclusion criteria

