1) A male/female adult aged between 20 and 75 years 2) Race: Asian 3) Eastern Cooperative Oncology Group performance status 0–2 4) Pathologically confirmed rectal cancer (rectal cancer located 10 cm or low from the anal verge in pelvis MRI) 5) Histologic type: adenocarcinoma, mucinous carcinoma, and signet ring cell carcinoma 6) Locally advanced rectal cancer with one or more of the following factors based on pelvis MRI: cTanyN1-2, cT3-4N0, or presence of extramural vascular invasion 7) MRI findings such as pelvic lymph node metastasis, anal sphincter invasion, and T4b are not included in the exclusion criteria, which cases will be enrolled by the researcher’s discretion 8) Patients with appropriate organ (bone marrow, kidney, liver) function 9) A person who understands the study and willing to provide informed consent	1) Colon cancer or rectal cancer located more than 10 cm from the anal verge 2) Stage I rectal cancer (clinical stage cT1-2N0) 3) Clinically or pathologically diagnosed distant metastasis (cTanyNanyM1) 4) Familial adenomatous polyposis 5) Hereditary nonpolyposis colorectal cancer 6) History of chemotherapy or radiotherapy within 6 months 7) History of colorectal cancer or other malignant tumors within 5 years 8) Currently under treatment of malignant tumors (except for cured nonmelanoma skin or in situ cervical cancer) 9) Comorbidities that make it difficult to undergo chemotherapy or radiotherapy 10) Bone marrow suppression with neutrophil count < 2 × 10^9^/L or platelet count < 100 × 10^9^/L prior to the first chemotherapy 11) Peripheral sensory neuropathy with functional impairment (grade 2 or higher) 12) Severe renal function impairment (creatinine cleaning rate 30 ml/min or less) 13) Severe hepatic dysfunction 14) Genetic problems such as galactose intolerance, Lapp lactase deficiency, or glucose-galactose malabsorption 15) Taking tegafur, gimeracil, oteracil complex and those within 7 days of discontinuation 16) Taking sorivudine, brivudin 17) Significant heart disease or myocardial infarction within the last 6 months 18) Hereditary diseases or history of coagulopathy 19) Central nervous system disorders with disability or mental disorders 20) Pregnant or lactating women 21) Currently participating in other clinical trials or receiving research medication 22) Unhealed wounds, fractures, peptic ulcers, abscesses in the abdominal cavity 23) Active gastrointestinal bleeding 24) Active infection requiring injection with antibiotics 25) Emergency surgery 26) History of hypersensitivity to drug in the study protocol 27) Dihydropyrimidine dehydrogenase deficiency 28) Not willing to participate

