### Sample size calculation

The 3-year DFS following preoperative CRT is expected to be 70% based on literature [23–27]. We hypothesized that the experimental arm would have a 10% improvement in 3-year DFS compared with the control group. This corresponds to a hazard ratio of 0.626 between the two arms (experimental /control). Assuming an 80% statistical power, a one-sided alpha level of 0.05, a minimal accrual duration of 36 months, and a minimal follow-up of 36 months, a total of 113 events will be needed to observe the expected difference using the one-sided log-rank test. Assuming a 5% rate of patients who are not informative or lost to follow-up, a total of 364 patients will be enrolled in this study, with 182 patients in each group.

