### Statistical analysis

The primary endpoint will be analyzed according to the intention-to-treat principle in patients who are randomized and receive preoperative treatments. Secondary analyses will be conducted using the per-protocol principle, considering only patients with sufficient compliance with the protocol. The Kaplan–Meier curve will be used to analyze the survival outcomes and the log-rank test for the prognostic factors. The chi-squared test will be employed to compare categorical data between the two groups and Student’s *t*-test for continuous variables. The effect of covariates on the endpoints will be evaluated using the Cox proportional-hazards model. QoL, assessed using questionnaires, will be expressed as mean, standard deviation, median, minimum, and maximum values. A mixed model for repeated-measure analysis with the assumption of an unconstructed covariance structure will be applied for QoL comparison. Least-square mean estimates will be calculated for *post hoc* analyses to compare the two treatment groups at each time point and evaluate any changes from the baseline scores. All tests will be two-sided, and *P*-value < 0.05 will be considered to indicate statistically significant differences. This trial has no plan for interim analysis. Missing data for the primary endpoint will be censored at either the last assessment date or the trial deadline, whichever is earlier. Because the primary endpoint is presented as recurrence or not, there are no outlier data. If there are missing values for the secondary endpoints, the last observation carried forward method will be employed to impute for the missing data with the most recently available data, and the Grubb and Cochran tests will be adopted to determine outliers if suspected.

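### The one test linked to the primary DFS comparison uses no strata or covariates; it is valid and has its planned power, but stratifying by baseline MRI cT and cN would make it more efficient at almost no cost

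*Protocol article*

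**What the plan says.** All places are in the Methods of the protocol article.

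- **Sample size calculation.** The design is stated as "Assuming an 80% statistical power, a one-sided alpha level of 0.05", and 113 events are required "using the one-sided log-rank test". No strata or covariates are mentioned. This is the only place where a test is linked to the primary hypothesis.
- **Study population, screening, and randomization.** "Block randomization at a ratio of 1:1 will be performed and managed by the central clinical research coordinator". No stratification factor is named.
- **Table 1.** Eligibility is judged on pelvic MRI and needs at least one of "cTanyN1-2, cT3-4N0, or presence of extramural vascular invasion". T4b tumours and pelvic nodal disease may be enrolled at the researcher's discretion.
- **Statistical analysis.** The log-rank test is mentioned in connection with prognostic factors, and then: "The effect of covariates on the endpoints will be evaluated using the Cox proportional-hazards model". The covariates are not named. The section does not say whether the model contains treatment arm, or whether it bears on the primary comparison.

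**The concern.** The population is prognostically mixed, from node-negative cT3 to T4b, node-positive and EMVI-positive disease. The article's Discussion itself lists cT4, cN2 and extramural venous invasion among the high-risk features that defined another trial's population. Clinical T and N stage are known before randomization, yet nothing in the article commits the primary comparison to using them.

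Two things are at stake. First, when strong predictors of DFS exist, a stratified test is more powerful than an unstratified one for the same number of patients. Second, if an adjusted hazard ratio is reported later with covariates that were not fixed in advance, it is open to the charge that they were chosen after seeing the data.

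**Working it through.** **Inputs from the article (Sample size calculation):** control 3-year DFS 70%, a 10-point improvement, hazard ratio (HR) 0.626, one-sided alpha 0.05, power 80%, 36 months' accrual, 36 months' minimum follow-up, 113 events, 5% uninformative, 364 patients.

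**Assumed, because the article gives no figure:** prevalence and prognostic HR of the MRI factors.

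**1. Reproduce the plan's figure.**
- HR = ln(0.80)/ln(0.70) = 0.6256.
- Schoenfeld events = 4(1.645 + 0.842)²/(ln 0.626)² = 112.7, so 113. This matches exactly.
- Power at 113 events = Φ(√113/2 × 0.468 − 1.645) = 80.1%.

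The ordinary two-arm log-rank formula therefore gives the stated design with no adjustment.

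**2. Simulation set-up.** Evaluable patients are 364 × 0.95 ≈ 346. Accrual is uniform and survival is exponential within strata. The marginal 3-year DFS is held at 70% vs 80%. There are 4,000 trials per scenario, so each power has a Monte Carlo standard error of about 0.6 points. The mean event probability is 0.347, so about 0.347 × 346 = 120 events are expected. That is slightly above 113, and explains why power starts a little over 80%.

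**3. One binary factor, one-sided 0.05, unstratified → stratified** (gains taken before rounding):

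| Prognostic HR | Prevalence 30% | Prevalence 50% |
|---|---|---|
| 1.0 | 81.5 → 81.5 (0.0) | 82.3 → 81.7 (−0.6) |
| 1.5 | 79.8 → 80.8 (+1.0) | 81.3 → 81.8 (+0.5) |
| 2 | 80.2 → 81.7 (+1.6) | 81.2 → 82.2 (+1.0) |
| 3 | 80.2 → 84.1 (+3.9) | 79.7 → 83.4 (+3.7) |
| 4 | 79.1 → 85.5 (+6.4) | 79.1 → 85.1 (+6.0) |

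The ratio of squared mean Z statistics turns this into equivalent events: about 1% more at HR 1.5, 4% at HR 2, 12% at HR 3, and 19–23% at HR 4.

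**4. Two binary factors, prevalence 20% and 40%, one-sided 0.05:**

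| Prognostic HRs | Unstratified → stratified | Gain |
|---|---|---|
| 1.5 and 1.5 | 81.1 → 81.7 | +0.6 |
| 2 and 2 | 81.3 → 83.4 | +2.1 |
| 2.5 and 2 | 80.4 → 82.8 | +2.4 |
| 3 and 2.5 | 80.0 → 85.3 | +5.3 |

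With this simulation error, a gain should not be read to a tenth of a point; a rerun can move it by about a point.

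**5. Type I error.** With no treatment effect and a factor of HR 2 or 3, both tests reject at 4.8–5.1%. Both are valid.

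**6. Chance imbalance.** Take 346/2 = 173 per arm and an assumed prevalence of 40%. The standard deviation of the between-arm difference in prevalence is √(2 × 0.4 × 0.6/173) = 0.053. With a factor HR of 2, one standard deviation shifts the log HR by roughly 0.053 × 0.693 = 0.037. That is 0.037/0.468 ≈ 8% of the design effect; two standard deviations give about 16%. Stratifying on the factor removes most of this shift.

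**The case against.** The strongest reply is that this is silence in a condensed article. The words "unstratified" and "unadjusted" do not appear, and stratification factors and model covariates are commonly left to the full protocol or analysis plan. That stands: a reader might infer that randomization is known to be unstratified, or that the sponsor has rejected adjustment, and the article supports neither. What remains is narrower. The one test the article does link to the primary hypothesis is a plain log-rank test, and the Cox sentence gives covariates no stated role in comparing the arms.

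A reader might also infer that baseline information is ignored altogether. The article does plan a Cox model with covariates, and a model that includes arm would fit that sentence. The gap is that the model's content and purpose are not stated.

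A third tempting inference is that the trial loses power or is biased. It does not and is not. The design power was computed without adjustment and reproduces, and the unstratified test stays at about 79–82% in every scenario. Chance imbalance is already covered by its error rate. The weaker unadjusted effect is the usual difference between a marginal and a conditional HR, and the design hypothesis is itself stated on marginal 3-year DFS.

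Two practical objections also stand. The size of the gain depends wholly on assumed factor strength. And Table 1 asks for one or more MRI criteria, so the article does not establish that EMVI status is recorded for a patient who qualifies on cT or cN.

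The Statistical analysis section also says "All tests will be two-sided, and" which conflicts with the one-sided design. At two-sided 0.05, 113 events give 70.2% power. That is a separate matter and is not evidence for this point.

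**Conclusion.** The point holds as an efficiency and prespecification improvement, not as an error. The log-rank test in the sample size section is valid and has its planned 80% power at one-sided 0.05. Using cT and cN in the primary comparison would add about 0.5 to 2.4 points of power for prognostic HRs of 1.5 to 2.5, and about 4 to 6 points for HRs of 3 to 4. For a factor with no prognostic value the change was between 0 and −0.6 points, no larger than simulation error. These figures assume binary factors at 20–50% prevalence, proportional hazards within strata, and 346 evaluable patients. The documents supply neither the strength nor the prevalence of the factors, so where this trial falls in the range cannot be settled from them.

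**What to change.** Before outcome data are seen by arm, state in the protocol or analysis plan:

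- **Primary test:** log-rank test stratified by baseline MRI cT (T4 vs lower) and cN (positive vs negative), plus any factor the full protocol uses to stratify randomization.
- **Matching estimate:** Cox HR for arm, adjusted for the same factors, and for EMVI if it is recorded for all patients.
- **Sensitivity analyses:** unstratified log-rank test and unadjusted HR.
- **Sparse strata:** a pooling rule, if randomization turns out to be stratified by hospital. Four cT-by-cN cells across nine hospitals make 36 strata for 113 events, about three events each.

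If the full protocol or analysis plan already says this, confirming it and aligning the wording is enough.

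The cost is analysis wording only, with no new patients, visits or data. Half the planned patients (182 of 364) had been recruited by July 2023 and no interim analysis is planned, so at the time of the article the factors could still be fixed before any comparison by arm. The small downside is that the adjusted HR is conditional on the chosen factors, so the unadjusted HR should be shown beside it.

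### The trial is sized for a one-sided 0.05 log-rank test but every test is declared two-sided at 0.05, so 113 events give about 70% power, not the stated 80%

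*Protocol article*

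**What the plan says.** The Sample size calculation section of the protocol article sets the design of the primary comparison: "Assuming an 80% statistical power, a one-sided alpha level of 0.05". It assumes 70% three-year DFS on chemoradiotherapy and that "the experimental arm would have a 10% improvement in 3-year DFS compared with the control group", which it converts to a hazard ratio of 0.626. From these inputs, with 36 months of accrual and 36 months of minimum follow-up, it concludes that "a total of 113 events will be needed to observe the expected difference using the one-sided log-rank test". A 5% allowance for uninformative or lost patients leads to 364 patients, 182 per arm.

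The Statistical analysis section opens with the analysis population for the primary endpoint, goes through the methods for survival, categorical, continuous and quality-of-life data, and then sets one general rule: "All tests will be two-sided", with P < 0.05 as significant. It exempts no test. It also states that no interim analysis is planned, so the final test carries the whole type I error.

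**The concern.** A one-sided 0.05 test and a two-sided 0.05 test have different critical values (z = 1.645 and 1.960), so only one of them can decide the primary comparison. The article states both, in adjacent sections, and nothing elsewhere in it reconciles them. The Study setting section calls the trial a superiority phase II trial but gives no alpha or sidedness.

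Two things are at stake. First, if the analysis rule is applied as written, the trial does not have the power on which its size was justified. Second, there is a band of results that one section calls positive and the other negative. With a single primary test and no interim look, that threshold decides the trial. Leaving it open allows the choice to be made, or to appear to have been made, after the data are known.

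**Working it through.** **Inputs.** From Sample size calculation: three-year DFS 70% (control) and 80% (experimental); hazard ratio (HR) 0.626; one-sided alpha 0.05; power 80%; 113 events; 1:1 allocation; 36 months' accrual and 36 months' minimum follow-up; 5% loss; 364 patients. From Statistical analysis: two-sided, P < 0.05, all tests. Normal quantiles: 1.645 (one-sided 0.05), 1.960 (two-sided 0.05), 0.842 (80% power).

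**1. The plan's hazard ratio.** ln(0.80)/ln(0.70) = 0.6256, which rounds to the stated 0.626. |ln 0.626| = 0.468.

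**2. The plan's event count.** Schoenfeld's formula for 1:1 allocation is d = 4(z_alpha + z_beta)² / (ln HR)².

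| Test | Schoenfeld, HR 0.6256 | Schoenfeld, HR 0.626 | Freedman (rounded up) |
|---|---|---|---|
| One-sided 0.05 | 112.4 → 113 | 112.7 → 113 | 117 |
| Two-sided 0.05 | 142.7 → 143 | 143.1 → 144 | 148 to 149 |

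Of these variants, only the one-sided Schoenfeld calculation gives the stated 113. The arithmetic in the sample size section is therefore right for a one-sided test and for no other.

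**3. Power with 113 events.** Power = Φ(√d/2 × |ln HR| − z_alpha). With d = 113 and HR 0.626, √113/2 × 0.4684 = 2.490.

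- One-sided 0.05: Φ(2.490 − 1.645) = Φ(0.845) = 80.1%.
- Two-sided 0.05: Φ(2.490 − 1.960) = Φ(0.530) = 70.2%.

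With the unrounded HR the figures are 80.2% and 70.3%. On Freedman's form the two-sided figure is 68.6% to 68.7%.

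**4. Critical hazard ratio.** The largest observed HR that reaches significance is about exp(−2 z_alpha/√d). With 113 events:

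- One-sided 0.05: exp(−3.290/10.630) = 0.734.
- Two-sided 0.05: exp(−3.920/10.630) = 0.692.

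An observed HR from about 0.69 to 0.73 changes verdict with the rule.

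**5. Events likely at the planned follow-up.** The article gives 113 as the number needed and does not say that it triggers the analysis. I assume exponential DFS, uniform accrual and 364 × 0.95 ≈ 346 evaluable patients. Accrual is either the planned 36 months or about 45 months, since the Current status section reports 182 patients between September 2021 and mid-July 2023, half the target in roughly 22.5 months. At 36 months' minimum follow-up:

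| Accrual | Mean event probability | Events in 346 | Two-sided power | Critical HR, two-sided / one-sided |
|---|---|---|---|---|
| 36 months | 0.347 | 120 | 73% | 0.70 / 0.74 |
| 45 months | 0.369 | 127 | 75% | 0.71 / 0.75 |

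The shortfall becomes 5 to 7 points but does not close.

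**6. When the two-sided target would be met.** On the same assumptions, 346 evaluable patients reach 143 events at a minimum follow-up of about 49.6 months (36-month accrual) or 45.4 months (45-month accrual), and 144 events roughly 0.6 months later.

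**The case against.** The strongest reply is that the specific rule overrides the general one. Only the sample size section names the test for the between-arm DFS comparison, "using the one-sided log-rank test". The analysis section mentions the log-rank test only in connection with prognostic factors, and its two-sided sentence follows a list of other methods and reads like a standard closing line. On that reading the primary test is one-sided at 0.05, the 80% power stands, and the article merely lacks an exemption. One-sided 0.05 is also a defensible choice for a phase II trial, and a statistical analysis plan that is not shown may already settle the matter.

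This is probably what was intended, and it means that the loss of power is conditional on the reading. It does not remove the conflict. The rule covers all tests, in a section that begins with the primary endpoint. An unseen analysis plan can agree with only one of the two statements, so the other would still be wrong. Nor is this a detail lost in condensing a longer protocol: both rules are stated outright.

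Three further points stand. The 70% figure applies at exactly 113 events, and 73% to 75% is the better estimate if the analysis follows 36 months' minimum follow-up. The disputed HR band moves up slightly with more events. The dates for reaching 143 to 144 events assume a constant hazard beyond three years, which the article does not state. If the hazard falls, those events come later or may not come within follow-up.

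**Conclusion.** The concern holds. The two sections contradict each other on the sidedness of the only primary test. The sizing arithmetic is correct for the one-sided test, but the stated 80% power does not hold under the analysis rule as written. At HR 0.626 and two-sided 0.05, power is about 70% with 113 events, so the chance of missing the targeted effect rises from 20% to about 30%. These figures need only the article's own inputs and the usual log-rank approximation. The milder figure of 73% to 75% rests in addition on exponential DFS, uniform accrual and 346 evaluable patients. This must be corrected before any comparative look at the data, because it determines which results count as success.

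**What to change.** State one rule in both sections of the protocol and in the statistical analysis plan, before any comparison by arm. The options are:

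1. **Keep the design (simplest).** Replace the general sentence in Statistical analysis with: *The primary DFS comparison is a one-sided log-rank test at the 0.05 level (equivalent to two-sided 0.10), reported with a two-sided 90% confidence interval for the hazard ratio; all other tests are two-sided at 0.05.* The 113 events, 364 patients and 80% power stay as they are. Cost: one sentence.
2. **Use two-sided 0.05 for the primary test and accept the power.** In Sample size calculation, replace the one-sided design with the two-sided test and restate power as about 70% with 113 events. Cost: a less favourable power figure, no extra patients.
3. **Use two-sided 0.05 and keep 80% power.** Set the analysis at 144 events (143 with the unrounded HR). Under the constant-hazard assumptions above, the same 364 patients reach this at roughly 45 to 50 months' minimum follow-up, inside the planned five years after surgery. Cost: a later primary analysis, and a risk that the events come more slowly than assumed. If the follow-up and event fraction were held fixed instead, about 364 × 144/113 ≈ 464 patients would be needed.

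The first two options are nearly free and rest on no assumption about late events.

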### Endpoints

The primary endpoint is the 3-year DFS, which is measured from the time of randomization until locoregional failure, metastasis, secondary cancer, or all-cause mortality. The data of patients who have not experienced any events by the time of the analysis will be censored at the last follow-up date. The Kaplan-Meier method will be used to calculate the survival rates. The secondary endpoints are the pathological complete response (pCR) rate; proportions of pathologic tumor regression grade (TRG) (Dworak [12], Mandard [13], AJCC TRG system [14]; R0 resection (microscopically clear resection) rate, 60-day postoperative surgical morbidity and mortality; treatment-related toxicity using the Common Terminology Criteria for Adverse Events version 5.0 (CTCAE v5.0); compliance with the study protocol defined as the completion of preoperative treatment, surgery, and adjuvant treatment; TRG based on magnetic resonance imaging (MRI) [15]); quality of TME [16]; 5-year DFS; 3/5-year overall survival (OS); loco-regional recurrence; distant metastasis; 3-year peripheral neuropathy grade (CTCAE v5.0); questionnaires of quality of life (QoL) using the Korean version of the European Organization for the Research and Treatment of Cancer Quality of Life Questionnaire Core 30 (EORTC QLQ-C30) version 3.0 [17]; QLQ-CR29 [18]; Low Anterior Resection Syndrome (LARS) score [19]; 5-item version of the International Index of Erectile Function (IIEF-5) [20]; retrograde ejaculation from inclusion to 2 years after surgery; and cost-effectiveness (direct cost, indirect cost, and quality-adjusted life-year).

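### The Statistical analysis section describes the primary endpoint as recurrence yes or no and does not carry over the log-rank test of DFS on which the trial was sized

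*Protocol article*

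**What the plan says.** Three sections of the Protocol article describe the primary endpoint or its test.

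- **Endpoints:** "The primary endpoint is the 3-year DFS, which is measured from the time of randomization until locoregional failure, metastasis, secondary cancer, or all-cause mortality". On censoring: "The data of patients who have not experienced any events by the time of the analysis will be censored at the last follow-up date". Kaplan-Meier is named for the rates, and DFS at 5 years appears separately among the secondary endpoints.
- **Sample size calculation:** "The 3-year DFS following preoperative CRT is expected to be 70% based on literature", with a 10-point improvement hypothesized. This is converted to a hazard ratio of 0.626 and to 113 events for a one-sided log-rank test at 0.05 with 80% power, given "a minimal accrual duration of 36 months, and a minimal follow-up of 36 months".
- **Statistical analysis:** "Missing data for the primary endpoint will be censored at either the last assessment date or the trial deadline, whichever is earlier". The next sentence begins: "Because the primary endpoint is presented as recurrence or not, there are no outlier data". Kaplan-Meier curves are for survival outcomes, and "the log-rank test for the prognostic factors". The chi-squared test is for categorical data between the groups. All tests are to be two-sided. No test is named for the comparison of DFS between arms.

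**The concern.** The yes/no description conflicts with the rest of the document in two ways. Recurrence leaves out deaths without recurrence and second cancers, both of which the Endpoints section counts. A yes/no outcome also has no censoring, yet the sentence just before it says how the endpoint is censored.

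The log-rank test appears in the analysis section only for prognostic factors, so the section an analyst would follow does not repeat the test that was sized. The 3-year label, next to a separate 5-year DFS, then leaves room for a comparison of 3-year rates. That comparison uses fewer events than the log-rank test on all follow-up and has less power. If the choice stays open, it could be made after the results are known.

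**Working it through.** **Inputs from the Sample size calculation:** 3-year DFS 70% and 80%; one-sided 0.05; power 80%; accrual 36 months; minimum follow-up 36 months; 5% loss; 364 patients, 182 per arm. Evaluable after loss: 364 × 0.95 = 345.8, about 346, or 173 per arm.

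**Assumptions not in the document:** exponential DFS and uniform accrual. The lower figure in each range treats the 5% as contributing nothing (346 patients); the upper counts all 364.

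**1. The plan's own figure.** HR = ln 0.80 / ln 0.70 = 0.2231 / 0.3567 = 0.626. Events (Schoenfeld) = 4 × (1.645 + 0.842)² / (ln 0.626)² = 4 × 6.185 / 0.2194 = 112.8, so 113. The stated figure reproduces.

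**2. Log-rank test on all follow-up.** With S the 3-year DFS, follow-up spread evenly over 36 to 72 months gives an event probability of 1 − (S − S²) / (−ln S).
- Control: 1 − (0.70 − 0.49) / 0.3567 = 0.411
- Experimental: 1 − (0.80 − 0.64) / 0.2231 = 0.283
- Mean 0.347, so about 120 events (346 patients) or 126 (364 patients)
- One-sided power = Φ(√events × 0.469 / 2 − 1.645): Φ(2.570 − 1.645) = 82% and Φ(2.636 − 1.645) = 84%

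If the 5% loss is read as annual, 364 patients give 113.6 events and 80%. On any of these readings the stated 113 events and 80% are supported.

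**3. Comparison of 3-year rates.**
- Events by 36 months: 173 × (0.30 + 0.20) = 86.5, or 182 × 0.50 = 91
- 173 per arm: SE = √((0.21 + 0.16) / 173) = 0.0462; z = 0.10 / 0.0462 = 2.16; one-sided power Φ(2.16 − 1.645) = 70%
- 182 per arm: SE = 0.0451; z = 2.22; one-sided power 72%

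**4. Sidedness, kept separate.** Replacing 1.645 by 1.960:

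| Comparison | Events | One-sided 0.05 | Two-sided 0.05 |
|---|---|---|---|
| Log-rank, all follow-up | 120–126 | 82–84% | 73–75% |
| Log-rank at exactly 113 events | 113 | 80% | 70% |
| 3-year rates | 86.5–91 | 70–72% | 58–60% |

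The choice of endpoint accounts for the step down the one-sided column. The step across the table comes from the conflict between one-sided planning and two-sided testing, and it affects the log-rank test as well.

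**5. Recurrence only.** This endpoint would have fewer events than DFS. The document gives no rate of death without recurrence or of second cancer, so the loss cannot be calculated.

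**The case against.** The strongest reply is that the document already points to one reading. DFS is defined as a time to event, neither censoring rule stops at 36 months, and the Sample size calculation names the log-rank test, the hazard ratio and the event count. The recurrence sentence explains why no outlier test is needed and does not specify an analysis. The chi-squared test is never assigned to DFS. An article also condenses, and details may sit in documents not shown. Most of this stands, and it limits the severity. It does not remove the contradiction, because the analysis section states an endpoint that differs from the defined one and gives the log-rank test another purpose.

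A reader might go further and infer that only the log-rank test on all follow-up can reach 113 events, and that every other reading has 58% to 70% power. The document does not support that:

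- The recurrence wording carries no 3-year limit. A yes/no comparison of any DFS event up to the data cut-off has the same 120 or so events. The difference is 0.411 − 0.283 = 0.128, SE = √((0.411 × 0.589 + 0.283 × 0.717) / 173) = 0.0507, z = 2.53, and one-sided power is about 81%. Its weakness is that it ignores unequal follow-up and censoring.
- A log-rank test truncated at 36 months appears nowhere in the text, and neither censoring rule contains such a cut.
- The 58% combines the endpoint question with the separate conflict over sidedness.

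Nor does the analysis section, as written, prescribe a binary or 3-year comparison. It only leaves room for one.

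**Conclusion.** The concern holds as an inconsistency in how the primary endpoint and its test are specified. The recurrence wording contradicts the DFS definition and the adjacent censoring sentence, and the log-rank test that was sized is not carried into the analysis section.

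Of the readings left open, the comparison of 3-year rates has a calculable cost: about 70% to 72% one-sided power instead of the stated 80%. This rests on the plan's 70% and 80%, with 173 to 182 informative patients per arm. The contrast with 82% to 84% for the log-rank test also rests on exponential DFS and uniform accrual. A recurrence-only endpoint would lose events in an amount the document does not allow one to state.

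This should be corrected, but it is not a fault that the trial cannot proceed with, because the Endpoints and Sample size sections already indicate the log-rank test.

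**What to change.** In the Statistical analysis section:

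- State that the primary comparison is the log-rank test of DFS between arms, with every event type listed under Endpoints and all follow-up to a data cut-off at which the last patient has completed the 36-month minimum. Report the hazard ratio and confidence interval from a Cox model.
- Make the Kaplan-Meier 3-year DFS by arm, with confidence intervals, a supportive estimate.
- Delete the recurrence description.
- State the sidedness of the primary test so that it and the required event count agree with the Sample size calculation.

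An event-driven cut-off is not needed for this. Under the assumptions above, the log-rank test is expected to have about 120 to 126 events at the planned cut-off (113.6 if the 5% loss is annual).

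The first three changes cost wording only. So does the fourth if the one-sided 0.05 level is kept. A two-sided 0.05 level at 80% power needs about 143 to 144 events (4 × (1.960 + 0.842)² / (ln HR)²), more than the planned cut-off is expected to yield. The sponsor would then have to revise the plan or state the lower power. The article reports 182 of 364 patients recruited by July 2023 and no planned interim analysis, so on the published status the wording could be settled before any outcome comparison.
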